## Abstract

This paper introduces the TRANSFORM project, which aims to improve access to mental health services for people with serious and enduring mental disorders (SMDs – psychotic disorders and severe mood disorders, often with co-occurring substance misuse) living in urban slums in Dhaka (Bangladesh) and Ibadan (Nigeria). People living in slum communities have high rates of SMDs, limited access to mental health services and conditions of chronic hardship. Help is commonly sought from faith-based and traditional healers, but people with SMDs require medical treatment, support and follow-up. This multicentre, international mental health mixed-methods research project will (a) conduct community-based ethnographic assessment using participatory methods to explore community understandings of SMDs and help-seeking; (b) explore the role of traditional and faith-based healing for SMDs, from the perspectives of people with SMDs, caregivers, community members, healers, community health workers (CHWs) and health professionals; (c) co-design, with CHWs and healers, training packages for screening, early detection and referral to mental health services; and (d) implement and evaluate the training packages for clinical and cost-effectiveness in improving access to treatment for those with SMDs. TRANSFORM will develop and test a sustainable intervention that can be integrated into existing clinical care and inform priorities for healthcare providers and policy makers.

Twelve per cent of the global disease burden is due to mental and behavioural disorders^1^ and more than 70% of this is experienced in low- and middle-income countries (LMICs).^2^ In Nigeria 12.1% of people have a lifetime rate of at least one DSM-IV disorder^3^ and in Bangladesh 16.1% of adults are estimated to suffer from some form of mental health problem.^4^ The mental health treatment gap, i.e. the difference between the number of people who need care and those who receive it, is reported at 80% for Nigeria, implying that only two out of every ten Nigerians with serious and enduring mental disorders (SMDs – defined as schizophrenia and other psychotic disorders, and severe mood disorders, often with comorbid substance misuse) are able to access care;^5^ in Bangladesh it is 92.3%, suggesting that fewer than one in ten who need mental healthcare are able to access it.^6^ In most LMICs public mental health systems do not receive adequate investment. For instance, in Bangladesh 2.64% of gross domestic product (GDP) is spent on health, which is the lowest in the South Asia region,^7^ and of the overall annual health budget, only 0.05% is designated for mental health.^8^ Yet the world's population living in slums reached 1 billion in 2018, and is projected to hit 3 billion by 2030, with the majority located in LMICs where the treatment gap is already huge.^9^

Help-seeking for SMDs in LMICs is pluralistic, with traditional and faith healers often being the initial, and sometimes the only, port of call (e.g.^10^). The preferred first contact for mental disorders is traditional and faith-based healers for 69% of adults in Nigeria^11^ and 30% in Bangladesh.^12^ Traditional or faith-based healing may alleviate symptoms in mood and anxiety disorders^13^ and provide valued social and spiritual support, but very little evidence exists that such practices improve care or outcomes for SMDs.^13–15^ On the contrary, reliance on traditional or faith-based systems can lead to treatment delays and poorer outcomes for people with psychotic illnesses.^16^ In many cases and across LMICs, it can also lead to coercion, including physical restraint, and human rights abuses.^17^

Within its Mental Health Gap Action Programme (mhGAP) the World Health Organization (WHO) has developed an intervention guide^18^ that aims to reduce the treatment gap by training non-specialist practitioners to screen for mental disorders, including serious mental illness (SMI), and provide treatment and appropriate referrals where needed. mhGAP strongly recommends the local contextualisation of training,^19^ especially cultural understandings of mental illness, which are a major determinant of help-seeking,^20^ but a systematic review of mhGAP in LMICs found that such contextualisation remains a challenge.^21^ Attempts at local adaptation of mhGAP have mainly been small scale.^22,23^ Large, community-based, stakeholder-driven, ‘bottom-up’ approaches to developing and testing interventions that are community-owned and community-delivered are lacking across LMICs.

Increasing people's access to psychiatric services without first determining local sociocultural understandings of mental illness, its causes and local help-seeking is unlikely to produce meaningful and sustainable change in the outcomes of SMI in LMICs. We need a deeper understanding of contextually embedded explanatory models and social determinants of mental illness and how these affect pathways to care, before settling on a solution such as ‘co-location’ of biomedical care at sites where patients seek traditional/faith-based healing.^24^ There is limited evidence on delivery and effectiveness of such collaborations, despite previous attempts to promote collaborations between faith-based healers and mental health services.^25,26^

## Aims and objectives of TRANSFORM

The TRANSFORM project aims to improve outcomes of persons with SMDs through better access to effective biomedical care by developing an innovative collaborative care model between traditional/faith healers, mental health professionals, primary care practitioners and community health workers (CHWs). We will develop and test community-delivered identification and referral pathways that recognise and engage with the experiences of mental ill health, existing beliefs about causation and treatment, and pluralistic help-seeking of slum-dwellers in Dhaka (Bangladesh) and Ibadan (Nigeria).

One of the key outputs of our project will be an intervention co-developed with key community stakeholders, which will improve the care of people with SMDs while protecting their human rights and meaningfully engaging with traditional and faith-based healers. Establishing such collaborations is not without particular and context-specific challenges, including long-held beliefs about mental health and illness and the power differentials between traditional healers and biomedical practitioners.^27^ Our innovative, bottom-up approach, whereby intervention and training are co-developed by healers, primary care workers and mental health practitioners in a spirit of mutual respect, seeks to address these challenges and promote participatory inclusiveness from all stakeholders.

## Method

### Design

The TRANSFORM study's design, depicted in Fig. 1, comprises five interlinked but distinct work packages (WPs), with data collection beginning in the first quarter of 2022 and a proposed study completion date of August 2024. The study will be conducted in accordance with ethical principles that comply with the Declaration of Helsinki and the International Council on Harmonisation's Harmonised Tripartite Guideline for Good Clinical Practice (GCP). All participants will provide informed consent before entering the study.

**Fig. 1 fig01:**
[figure not shown]
An overview of the TRANSFORM work packages outlining each package's goals. WP, work package; CHW, community health worker; SMD, serious mental disorder (psychotic disorders and severe mood disorders, often with co-occurring substance misuse).

### Population

Our clinical population of interest are individuals (aged 18+) with SMDs living in deprived, urban neighbourhoods (slums) in Dhaka and Ibadan. Participants will be identified by healers and CHWs in WP4. We are not including individuals with a primary substance use disorder who do not have any SMD, as our pilot work has shown that people with substance use disorder do not seek traditional/faith healing and our intervention is therefore less likely to reach this specific population.

### Study sites

TRANSFORM brings together leading institutions across the UK, Asia, Africa and North America: the University of Warwick, UK; the National Institute of Mental Health and the Telepsychiatry Research and Innovation Network, Dhaka, Bangladesh; the University of Ibadan, Nigeria; and McGill University, Montreal, Canada.

We have chosen two sites, both in impoverished city areas, one in Dhaka, Bangladesh, and the other in Ibadan, Nigeria. These sites have been chosen because they both have well-established, well-patronised traditional healing services and well-developed mental health services within reach. At both sites, services offered by the CHWs and other primary and mental health services (both secondary and tertiary care) are typical of the traditional and faith-based healing pathways that operate in many LMICs. As a result, they provide an opportunity to test an integrated model and examine the barriers that arise from the very different ways in which traditional/local and universal/biomedical perspectives see the world. It cannot be assumed that integration will be unproblematic. Potential problems range from different epistemologies and taxonomies to perceived threats to livelihoods (e.g. competition for ‘customers’). There will also be social issues relating to gender, religion, identity, professional pride and autonomy, all of which may influence help-seeking for SMDs. Our project sites and our methodology offer an opportunity to understand these complex matters and provide sustainable solutions that have the potential to affect the understanding of, and attitudes towards, help-seeking for SMDs.

#### Ibadan, Nigeria

In Ibadan, the study will be conducted in the five urban local government areas (LGAs), which house adjacent and overlapping slum communities and have large numbers of traditional and faith healers who offer healing to people with SMDs. People predominantly of Yoruba ethnicity live in these five LGAs, which have a combined population of 1 338 659 inhabitants.^28^ Many practise religious syncretism through the combination of traditional African religions with Islam or Christianity. Several ancient and popular shrines, which serve as places for the treatment of mental illness, are found in the study area, alongside Islamic and Christian healing sites. Healing methods include divination, prayers and the use of herbal medicines. Apart from shrines, there are residential homes where people with mental illness stay to receive traditional healing. Many people with SMDs are homeless and roam around, especially in areas with reported high levels of psychoactive substance use and violence.

Nigeria operates a federal system with three tiers of government: a central administration, 36 states with their capital cities and 774 LGAs. In line with the three tiers of government, there are three tiers of healthcare delivery services: tertiary healthcare, provided principally by the federal government and consisting of specialised services in teaching and other specialist hospitals; secondary healthcare, provided in general hospitals run primarily by state governments; and primary healthcare, constitutionally the responsibility of local governments.

Basic healthcare services are provided in government-owned primary health clinics. There are between four and seven primary healthcare clinics in an LGA (district). The health workers who run the primary healthcare clinics are community health officers (CHOs) and community health extension workers (CHEWs), who are supposed to spend 70% of their time out of the primary healthcare centres and in the community. More infrequently, qualified public health nurses or midwives are also found in primary healthcare clinics. There are no dedicated mental health professionals at the primary healthcare level. Services are part of the public healthcare system and are ostensibly available free of cost. CHOs and CHEWs are permitted by law to identify, treat and prescribe medication for SMDs within the context of primary care using a standing order process. Owing to inadequate training and a lack of supervision, CHOs and CHEWs lack the capacity to manage persons with SMDs in primary healthcare and referrals are made to the nearest secondary or tertiary mental health centre.

The University College Hospital (UCH), Ibadan, a tertiary health centre (where the TRANSFORM investigators for Ibadan are based) is the flagship teaching hospital in Nigeria, with an array of clinical departments and specialist services, including psychiatry. This hospital is situated in the centre of an urban LGA close to the heart of the ancient city of Ibadan and is easily accessible by public transport. The Department of Psychiatry has 12 consultant psychiatrists, 30 resident doctors and a large multidisciplinary team consisting of psychiatric nurses, psychologists, social workers, occupational therapists and disability specialists. The hospital has 64 dedicated beds for adult psychiatry and an 8-bed adolescent in-patient unit. For persons without health insurance, healthcare is accessed by out-of-pocket payment.

The State Specialist Hospital, Ring Road Ibadan, at the secondary level of healthcare, is the second referral facility that is publicly run and provides specialist mental health services to the community. The government offers highly subsidised healthcare, so this hospital serves those who cannot afford care at the UCH. The facility has 20 beds for psychiatry, 3 psychiatrists, 2 medical officers, psychiatric nurses and social workers in the mental health unit.

#### Dhaka, Bangladesh

In Dhaka, the study will be conducted in the Korail Basti (*basti* meaning slum). Korail is one of the largest slums in Bangladesh, located in the centre of the city, encroaching on parts Dhaka's most affluent neighbourhoods. The area of the slum is claimed to be between 180 and 220 acres.^29^ The majority of Korail's population (estimated to be around 200 000)^30^ subsist below the poverty line and work in low-income jobs. They have limited access to the city's healthcare services and there is little connection with the surrounding major roads.^31^

There is widespread stigma related to mental illness in Bangladesh.^32^ Referrals of patients with SMDs to mental health specialists by primary healthcare providers are near non-existent, as are mental healthcare facilities.^33^ Many people living in the slums use traditional and faith-based healers. There are nine mosques within the Korail Basti, each with imams (Islamic priests) who are the ‘go-to people’ for mental health problems and support. One key religious healing practice is *Kalami* (a healing practice based on verses of the Qur'an). The healing aims to cure problems through communication with *jinn* (spirits), and treatments can also include giving patients *pani-pora* (blessed water) to exorcise the *jinn*.^34^

The National Institute of Mental Health (NIMH) is Bangladesh's leading public institution dedicated to the treatment of mental health problems, along with mental health policy formation, research and training of mental health professionals. The facility is located 7.3 km from the Korail Basti. It serves as one of the cheapest clinical options for the Korail community and employs over 300 personnel to deliver out-patient, in-patient and emergency medical services for child and adult mental disorders. As the largest psychiatric teaching hospital in the country, NIMH provides training in psychiatry, psychology and medicine as well as engaging in research activities and mental health policy formation.

NIMH has a total of 200 in-patient beds; 70% of these are non-fee-paying government-funded beds and the rest are private fee-paying beds. In-patient and out-patient admissions range across all units, including adult psychiatry and community and social psychiatry. In 2019, 58 846 patients were provided with service through the out-patient department.

Bangladesh has a pluralistic healthcare system where healthcare services are delivered by different public and private sectors, and we are also exploring ways to embed other referral systems in Dhaka as part of the study.

## Study delivery: proposed plan

### Work package 1: community-based ethnographic assessment (months 1–12)

In WP1, we will conduct a community-based ethnographic assessment using qualitative and participatory methods to explore local understanding of SMDs and help-seeking. We will use a variety of methods, including participatory mapping, free-listing and ranking exercises, walk-along interviews, observation and individual and natural group interviews to explore understandings and experiences of mental illness, poverty, daily life and the role of traditional and faith-based healing for SMDs, from the perspectives of people with lived experience of mental illness, caregivers, community members, healers, CHWs and health workers. Our findings will be used to co-design, with people with lived experience, caregivers, CHWs and traditional healing practitioners, training packages for screening, early detection and referral to mental healthcare for individuals (aged 18 and over) with SMDs. This will be used to develop a matrix of help-seeking pathways and barriers and enablers to mental healthcare.

### Work package 2: developing training packages for traditional/faith healers and community health workers; raising community awareness (months 12–18)

We will hold workshops with traditional/faith healers and CHWs to co-produce two training packages. The training package for healers will aim to help them identify signs of SMD in individuals who seek their care. We will identify best pathways for them to refer people with signs of SMD to the local primary care centre or to a CHW. The intervention will be designed not to replace faith and traditional healing practices with biomedical care, but rather to serve as a complement to their role.

For CHWs, we will modify the mhGAP intervention and guide^18^ based on local contextual factors identified through WP1 and based on previous work,^35^ including local taxonomies of mental illness and ideas on causation and help-seeking. The CHW training will upskill them to deliver community-based interventions, including screening and early identification of those with SMDs, psychoeducation, promoting medication adherence, referral and navigation to secondary care services, support for carers and community health promotion. It will also include a component pertaining to effectively liaising with traditional/faith healers, particularly for identifying those with SMDs who need additional care.

We will also co-produce media in various formats, such as posters and radio adverts, to engage communities with the intervention. The content and methods used will be informed by findings from WP1.

### Work package 3: piloting and implementing the training intervention (months 18–24)

We will introduce the training intervention and discuss how it can be used in day-to-day practice with CHWs, traditional healers, faith healers and primary care practitioners. In particular, traditional and faith healers will be trained as key informants who can offer people with SMDs and their caregivers the additional option of seeing a CHW. This will be in three phases:

#### Phase I: relationship-building

During this phase, we will discuss:
recognition of the pivotal role of healers within the community and the value of their contributionsthe challenges of recognising SMDs and providing high-quality, rights-based carethe importance of collaborating and working harmoniously for all stakeholders, particularly for people with SMDs and their caregivers.

#### Phase II: review of proposed training

This will cover:
an overview of the proposed plan and training contentwillingness or reluctance of traditional and faith healers and CHWs to embark on training and ways to overcome any challengesiterative development of training packages based on feedbackdealing with stigma of SMD, misperceptions about biomedical care and healers, financial constraints in accessing care, managing non-adherence to treatment or drop out from care, supporting households through psychoeducation and dealing with criseshelping patients and families navigate the referral pathwayuse of community resources to facilitate recovery, such as self-care, supported employment, activities of daily living.

#### Phase III: delivery of training

Findings from phases I and II above, in addition to content generated from WP2, will allow the further refinement of the training package; the referral pathway and the support for ongoing care; and the identification of trainers. Following the refinement of the training package, two half-day interactive training workshops will be delivered to traditional practitioners and CHWs, with a half-day supervision session every 3 months. All training materials and delivery will be in the local languages (Bengali in Dhaka, and Yoruba in Ibadan).

### Work package 4: community identification, referral and outcome assessment of people with SMDs (months 24–48)

Our aim for WP4 is to determine whether our interventions lead to an increase in numbers of people with SMDs accessing biomedical care. We will further ascertain these individuals’ initial and follow-up mental health status and quality of life, reduction in caregiver burden, and changes in community attitudes and help-seeking for SMDs. We will collect data pre-intervention to identify the number of people with SMDs attending mental health services from the study site and their basic clinical and sociodemographic characteristics. Data collection systems will be in place for baseline and follow-up assessments of successive patients identified with signs of SMD and enrolled into the study over 12 months.

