#### Quantitative evaluation

In WP4, we will adopt a two-fold approach. Primarily, we will assess the impact of the proposed intervention on the (mental health) care pathway of individuals with SMDs and its potential effect on their health status. We will assess impact on the referral pathway by comparing referral rates made to the participating healers 12 months before and after intervention (training) is delivered. We will undertake a pre–post regression analysis to quantify the referral difference at the healer level after adjusting for healers’ and patients’ characteristics. Both the crude and the adjusted rate change and its corresponding 95% confidence interval will be provided.^38^ The change in referral rate will be the primary outcome of interest for this study.

We acknowledge that some participants may be directed to biomedical services by a healer but, for various reasons, may not actually access biomedical care. To further evaluate the impact of a healer's referral, we will try our best to trace their referrals and find out whether potential participants used mental health clinics.

In addition to the primary outcome, a number of patient-related secondary outcomes will be analysed. At this (patient) level, analysis will focus on clinical outcomes, functioning, participant and family satisfaction, medication adherence and attendance for clinical follow-up (Table 1 outlines the measures and time points for assessments).Uptake of healthcare will be evaluated longitudinally: at baseline (i.e. intake) and at months 1, 2 and 3. Similarly, clinical outcomes will be assessed longitudinally using the Global Assessment of Symptoms (GAS), Global Assessment of Functioning (GAF) and clinician-rated primary and secondary diagnoses. Carer burden will be assessed at baseline and post-intervention at month 3 using the Perceived Family Burden Scale (PFBS), and family satisfaction will be assess longitudinally using the Verona Service Satisfaction Scale (adapted to LMIC contexts). We will investigate service utilisation and associated costs using the abbreviated version of the Client Services Receipt Inventory (CSRI) – modified as used in our previous study.^39^ We will employ a linear mixed model to estimate longitudinal changes, adjusting for patient characteristics, time and baseline values/scores. Estimates and effect sizes will be reported, together with their 95% confidence intervals.

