**Table 1 tab01:** Primary and secondary outcomes to be collected and their corresponding time points

		Assessment time point							
Domain	Tool	Pre-intervention	Baseline/intake	Month 1	Month 2	Month 3	Post-intervention	Analysis plan	Estimates reported
Number of individuals from study sites accessing biomedical care	Review of health record systems at NIMH in Dhaka (Bangladesh) and Ibadan (Nigeria)	✓					✓	Pre–post analysis	Referral rate and 95% CI
Number of referrals made by CHWs and traditional and faith healers	For each referral, CHWs will record date of referral and referral source (e.g. self, family member, faith or traditional healer)						✓	Pre–post analysis	Referral rate and 95% CI
Pathways to care (number and type of help-seeking contacts made prior to accessing biomedical care, and duration of untreated illness)	Nottingham Onset Schedule (NOS)		✓				✓	Pre–post analysis	Referral rate and 95% CI
Clinical characteristics of individuals accessing biomedical care	See assessment below	✓					✓	Longitudinal	Mean change since baseline
Sociodemographic profile									
	Age	✓	✓				✓	Longitudinal	Mean change since baseline
	Gender	✓	✓				✓	longitudinal	Mean change since baseline
	Education level		✓					Baseline only	descriptive only
	Religious background	✓	✓				✓	Longitudinal	Mean change since baseline
	Employment status		✓					Baseline only	Descriptive only
	Socioeconomic status		✓					Baseline only	descriptive only
	Family and marital status		✓					Baseline only	Descriptive only
	Area of residence	✓					✓	Longitudinal	Mean change
	Number of children <18 years old	✓	✓					Pre-intervention/baseline only	Descriptive only
Symptom severity	Global Assessment of Symptoms (GAS)		✓	✓	✓	✓		Longitudinal (baseline, months 1, 2 and 3)	Mean change (repeated measures)
Clinical/symptom profile	Clinician-rated primary and secondary diagnoses as recorded in charts		✓					Baseline only	Descriptive only
Level of functioning	Global Assessment of Functioning (GAF)		✓	✓	✓	✓		longitudinal (baseline, months 1, 2 and 3)	Mean change (repeated measures)
Physical health	Body mass index (BMI)		✓			✓		Longitudinal (baseline, month 3)	Mean change (repeated measures)
Carer burden	Perceived Family Burden Scale (PFBS)		✓			✓		Month 3 only	Descriptive only
Engagement with services	Record each month of whether patient contacted treatment provider and type of contact (phone, in-person, etc.).			✓	✓	✓		Longitudinal (months 1, 2 and 3)	Rate change (repeated measures)

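### The primary referral rate carries no diagnostic condition, so a rise in it would not by itself show that more people with SMD were reached; the intake diagnosis should be used to check this

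*Protocol article*

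**What the plan says.** All places are in the Protocol article.

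- **Aim.** Work package 4 is to determine whether more people with SMDs access biomedical care. The Population section likewise defines the target as adults with SMDs, and adds: "We are not including individuals with a primary substance use disorder who do not have any SMD". It says that healers and community health workers (CHWs) identify the participants.
- **Primary outcome.** Quantitative evaluation states: "The change in referral rate will be the primary outcome of interest for this study". The comparison is described as "comparing referral rates made to the participating healers 12 months before and after intervention (training) is delivered"; I read this as referrals made by healers, because the next paragraph speaks of a healer's referral. No diagnostic condition is attached.
- **What triggers a referral.** Under Work package 2, healers are trained to "refer people with signs of SMD to the local primary care centre or to a CHW".
- **What is recorded.** In the referral row of Table 1: "For each referral, CHWs will record date of referral and referral source". No diagnosis or screening result is named.
- **Patient cohort.** Work package 4 describes those assessed at baseline and follow-up as "successive patients identified with signs of SMD and enrolled into the study over 12 months". This sentence concerns the enrolled cohort, not the primary count.
- **Diagnosis.** Table 1 lists "Clinician-rated primary and secondary diagnoses as recorded in charts", ticked at intake alone and marked for descriptive reporting. The text of Quantitative evaluation instead puts it among the outcomes assessed longitudinally: "Global Assessment of Functioning (GAF) and clinician-rated primary and secondary diagnoses".

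**The concern.** The aim concerns people who have SMD; the primary outcome counts acts of referral prompted by signs. The two agree only if the share of referred people who truly have SMD stays about the same from before to after training.

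The intervention acts directly on the decision to refer. Training healers to recognise signs can improve detection, lower the threshold for referral, or both, and a raw referral rate cannot separate these. If the threshold falls far enough, the primary result improves while the number of people with SMD who are referred does not.

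The patient-level results (GAS, GAF, EQ-5D, medication adherence) face a related difficulty. They are meant to describe people with SMD, but the cohort is entered on signs, so some members may not have the condition. The direction of the resulting error is not known.

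The item that would settle both questions, the clinician's diagnosis, is already collected. The article gives it two incompatible roles, and neither is case confirmation.

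**Working it through.** **1. The passages side by side**

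| Element | Restricted to SMD? | Source |
|---|---|---|
| Aim | Yes | Work package 4 |
| Target population | Yes | Population |
| Pre-intervention service count | Yes, as worded in the text | Work package 4 |
| Primary outcome | No condition stated | Quantitative evaluation |
| Healer referral | On signs | Work package 2 |
| Fields per referral | Date and source | Table 1, referral row |
| Tracing of referrals | Clinic use only, best effort | Quantitative evaluation |
| Enrolled cohort | On signs | Work package 4 |
| Clinician diagnosis | Collected at intake; not used to confirm cases | Table 1; Quantitative evaluation |

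**2. Size of the possible distortion**

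The article gives no referral rate, expected effect or confirmed share, so there is no figure to reproduce. Everything below is assumed, to show the mechanism.

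Let R be the raw ratio of referrals (after/before, equal 12-month periods), and let p0 and p1 be the shares with SMD before and after training. Then

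SMD referral ratio = R × p1 / p0,

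which equals 1 when p1 = p0 / R.

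Take 100 referrals before training and p0 = 80%, which gives 80 people with SMD.

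| Referrals after | R | p1 = 80% | p1 = 60% | p1 = 50% | p1 = 40% | p1 giving no change |
|---|---|---|---|---|---|---|
| 125 | 1.25 | 1.25 | 0.94 | 0.78 | 0.62 | 64% |
| 150 | 1.50 | 1.50 | 1.12 | 0.94 | 0.75 | 53% |
| 200 | 2.00 | 2.00 | 1.50 | 1.25 | 1.00 | 40% |

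For example, 150 × 0.50 = 75 people with SMD against 80 before: 75 / 80 = 0.94. For the break-even share, 0.80 / 1.50 = 0.53.

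**3. Would the raw result look convincing?**

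Using SE(log R) = √(1/n0 + 1/n1) and ignoring clustering by healer, 100 against 150 gives √(1/100 + 1/150) = 0.129. The 95% interval is 1.50 × exp(±1.96 × 0.129), that is 1.16 to 1.93. For 100 against 200 it is 1.57 to 2.54. Both exclude 1, yet both are compatible with no gain in SMD referrals if the share falls to 53% or 40% respectively. Clustering would probably widen these intervals without changing the mechanism.

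**4. The opposite case**

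If training leaves the share unchanged, the raw ratio is undistorted (column p1 = 80%). If the share rises, say to 90%, the SMD ratio is 1.50 × 0.90 / 0.80 = 1.69, and the raw ratio understates the benefit.

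**The case against.** **Referral is a legitimate process outcome.** The intervention trains people to refer, so counting referrals is defensible. This stands, and it is why the raw rate can remain primary.

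**A reader might infer that the plan defines its primary count as anyone showing signs.** It does not say so. The sentence on enrolling people with signs describes the follow-up cohort, and the article states no rule for a countable referral. Such a rule may sit in the full protocol or in the dedicated SAP that the article announces. What the article does state is a primary outcome without a diagnostic condition, beside an aim that has one.

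**A reader might infer that over-referral would pass unnoticed as success.** That goes too far. CHWs are to be trained in screening, so the exclusion of primary substance use disorder need not rest on healers alone. Table 1 also has a before-and-after count of people accessing care from health records, which Work package 4 words for the earlier period as people with SMDs, and a before-and-after row on the clinical characteristics of attenders. A rise in referrals without a rise in SMD attendance could show there. These safeguards are partial: screening is not diagnosis, the Table 1 record row is not labelled as restricted to SMD, and neither measure is primary.

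**A reader might call diagnosis purely descriptive.** That is true of Table 1 only; the analysis text says otherwise, and the two must be reconciled.

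**A reader might want success to depend on a before/after ratio of confirmed referrals.** The listed data cannot support this. The referral row is ticked post-intervention only, chart diagnosis is ticked at intake only, and tracing is best effort. Gating the conclusion on that ratio could introduce a new bias from unequal ascertainment.

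**Conclusion.** The point holds in a limited form. As stated in the article, the primary outcome cannot by itself answer the Work package 4 question, because it does not distinguish more people with SMD being referred from more people being referred. The distortion arises only if the share with SMD falls after training. Nothing in the article shows that it will, and the error could run the other way.

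The size cannot be derived from the article. On the assumed starting share of 80%, a raw ratio of 1.50 corresponds to an SMD ratio between 1.50 (share unchanged) and 0.75 (share down to 40%), with break-even at 53%. All these shares are illustrative.

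Separately, and without any assumption, the article contradicts itself on diagnosis: a baseline descriptor in Table 1, a longitudinal outcome in the text. It should be corrected, because diagnosis is the variable best placed to close the gap between aim and outcome.

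**What to change.** Keep the raw referral rate as the primary outcome and make four additions.

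1. Beside it, report the number and share of post-training referrals with clinician-confirmed SMD. Show referrals without a diagnosis as a separate unconfirmed group, not as negatives.
2. In the before-and-after health-record review (first row of Table 1), count people with a recorded SMD diagnosis, using the same diagnostic categories in both periods. Base the conclusion about access for people with SMD on this count together with the referral rate.
3. Analyse the patient-level outcomes in those with confirmed SMD, with all enrolled patients as a sensitivity analysis.
4. Reconcile the text of Quantitative evaluation with Table 1 by treating diagnosis as a baseline classifier and removing it from the longitudinal outcomes.

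Do not make success depend on a before/after ratio of confirmed referrals, since no diagnosis is planned for referrals made before training.

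The cost is some protocol wording and a little more analysis of data largely planned already. Item 2 assumes that the records hold a usable diagnosis in both periods, which the planned pre-intervention count of people with SMDs already requires. Some referrals will stay unconfirmed because tracing is best effort, so the confirmed number will be a minimum, and the share should be given both among all referrals and among those assessed.
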